### Participant timeline {13}

#### Enrollment

The main examiner (anesthesiology specialist) suggests patient participation in the trial by oral interview. Patients fulfilling the inclusion criteria and not meeting the exclusion criteria will be offered the participation in the trial when a decision of a sternotomy by surgeon is achieved.

#### Assessments and visits

Daily visits to the participants will be conducted by a cardiac surgeon while in the hospital for whole period of hospitalization to evaluate relevant outcome measures. The cardiac surgeon will examine the sternotomy for possible complications. All the biochemical examinations are indicated by any medical doctor in the cardiac surgery ward (anesthesiology specialist, cardiology specialist, or cardiac surgeon). The last evaluation will be done on the day of discharge, then after in the sixth week and in the sixth month after cardiac surgery (including sternotomy).

Participant timeline is displayed in Table 4.

**Table 4 Tab4:**
[figure not shown]
Participant timeline in REINFORCE-D clinical trial

### Sample size {14}

To determine the optimal trial patient population, a sample size calculation was made. This calculation is based on the estimated incidence of sternotomy healing complications, which is typically around 5% at our cardiac surgery center (unpublished internal data). This is in agreement with data published previously. If we assume the same incidence during the trial, and considering vitamin D supplementation, we expect an incidence of roughly 1%. Thus, 284 patients are needed in the placebo arm and 284 patients in the treated arm, considering a one-sided statistical alternative. We plan to enroll approximately 300 patients in each arm, altogether 600 patients.

MedCalc software (version 17.8.6) was used to calculate sample size. The following input data was used for sample size calculation:
*p*1 = 0.05, incidence of event occurrence (sternotomy complications) in the placebo arm*p*2 = 0.01, incidence of event occurrence (sternotomy complications) in the treatment arm (cholecalciferol)α = 0.05, probability of type I errorβ = 0.2, probability of type II error

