## Statistical methods

### Statistical methods for primary and secondary outcomes {20a}

In the statistical analysis of the primary endpoint, it will be necessary to ascertain whether the incidence of all sternotomy complications (6 months follow-up) differs significantly between the treatment and placebo groups. Data will be expressed as number of patients with or without sternotomy healing complications in the placebo/cholecalciferol groups. The chi-square test will be used for this analysis.

Data of all secondary endpoints will be expressed as arithmetic average ± standard deviation. To analyze these data, a two-group *t* test will be used.

This clinical trial assumes a significance level of 0.05. The software MedCalc (version 17.8.6.) will be used for statistical calculations.

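### The 284 per arm is labelled one-sided, but at the stated alpha of 0.05 it is the two-sided figure, so the primary success threshold is left in doubt

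*Protocol article*

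**What the plan says.** Sample size {14} in the protocol article lists four inputs: placebo incidence 0.05, cholecalciferol incidence 0.01, type I error 0.05 and type II error 0.2. From these it states: "Thus, 284 patients are needed in the placebo arm and 284 patients in the treated arm, considering a one-sided statistical alternative". It then rounds up for enrolment: "We plan to enroll approximately 300 patients in each arm, altogether 600 patients".

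Statistical methods {20a} sets the primary analysis. A chi-square test is to show whether the complication incidence "differs significantly between the treatment and placebo groups". On the error rate it says only: "This clinical trial assumes a significance level of 0.05". It gives no direction, and it does not mention a one-sided p-value.

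Objectives {7} words the primary hypothesis directionally, as a reduction on cholecalciferol. Sequence generation {16a} gives 1:1 allocation.

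**The concern.** A one-sided test needs fewer patients than a two-sided test at the same alpha. A figure of 284 per arm for a fall from 5% to 1% at 80% power looks too large for one-sided 0.05 and about right for two-sided 0.05.

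If so, the only explicit statement of sidedness in the document is contradicted by its own arithmetic, and it points the opposite way from the chi-square test in {20a}. A reader who follows {14} would call the trial positive at z above 1.645. A reader who follows {20a} would need 1.96. With few events expected, a result can fall between the two thresholds. If the question is still open at unblinding, the threshold could be chosen after the result is known.

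**Working it through.** **Inputs** (all from {14}, except allocation from {16a}): p1 = 0.05, p2 = 0.01, alpha = 0.05, power = 0.80, ratio 1:1. The mean rate is (0.05 + 0.01)/2 = 0.03, and the difference is 0.04.

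**Formula** (pooled variance under the null, per arm):

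n = [z_α·√(2·0.03·0.97) + z_β·√(0.05·0.95 + 0.01·0.99)]² / 0.04²

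The two roots are √0.0582 = 0.2412 and √0.0574 = 0.2396, and z_β = 0.8416.

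- **Two-sided 0.05** (z_α = 1.960): (0.4728 + 0.2016)² / 0.0016 = **284.3**. This is the protocol's 284, rounded to the nearest integer. Rounding up would give 285.
- **One-sided 0.05** (z_α = 1.645): (0.3968 + 0.2016)² / 0.0016 = **223.8**, so 224 per arm.

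**Could another formula give 284 one-sided?** Per arm, rounded up:

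| Method | One-sided 0.05 | With continuity correction | Two-sided 0.05 | With continuity correction |
|---|---|---|---|---|
| Pooled variance | 224 | 272 | 285 | 333 |
| Unpooled variance | 222 | 270 | 282 | 331 |
| Pooled in both terms | 225 | 273 | 286 | 335 |
| Arcsine | 197 | 245 | 250 | 298 |

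An exact one-sided Fisher test already has 80.1% power at 250 per arm. The closest one-sided figure is 273, which is 3.9% below 284. Three uncorrected two-sided figures (282, 285, 286) lie within two patients of 284. One-sided alpha of 0.025 uses the same z_α as two-sided 0.05 and so gives the same number, but the printed alpha is 0.05.

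**Power at the stated and planned sizes** (normal approximation; exact figures are for the uncorrected chi-square test):

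| Per arm | Two-sided 0.05 | Exact | One-sided 0.05 | Exact |
|---|---|---|---|---|
| 284 | 79.96% | 84.4% | 87.6% | 90.5% |
| 300 | 82.1% | 86.4% | 89.2% | 91.9% |

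At 284 the normal approximation meets the 80% target under the two-sided reading. Under the declared one-sided reading the power would be about 88%. With Fisher's test the exact power at 284 is 76.9% two-sided and 85.6% one-sided.

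**Does the choice change a conclusion?** At 300 per arm and 5% placebo incidence, 300 × 0.05 = 15 placebo events are expected. With 7 events on cholecalciferol, the difference is 8/300 = 0.0267, the pooled rate is 22/600 = 0.0367, and the standard error is √(0.0367 × 0.9633 × 2/300) = 0.01535. That gives z = 1.74.

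| Placebo vs cholecalciferol events | One-sided p | Two-sided p |
|---|---|---|
| 14 vs 6 | 0.034 | 0.069 |
| 15 vs 7 | 0.041 | 0.082 |
| 16 vs 7 | 0.028 | 0.056 |

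Each is positive under one rule and negative under the other. The zone is narrow: with 15 placebo events, 6 on treatment gives z = 2.00 (positive under both) and 8 gives z = 1.49 (negative under both). If the planned effect held exactly (15 vs 3), z would be 2.87, so the choice would not matter. It matters if the effect is smaller than planned.

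**The case against.** The strongest reply is that {14} only explains how the number was obtained, while the analysis rule is in {20a}. A chi-square test on a 2×2 table is non-directional unless someone modifies it, so there is one analysis rule and one mislabelled planning phrase. The alpha of 0.05 is the same in both sections. The trial is not undersized on its own assumptions. The doubling of the false-positive rate occurs only if the sponsor actually tests one-sided at 0.05, which {20a} does not say. Explicit sidedness of the test may be left to an analysis plan that is not shown. Finally, one-sided 0.025 would also preserve 284 and would suit the directional hypothesis in {7}.

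Much of this stands. Enrolment is unaffected, {20a} does not itself prescribe a one-sided test, and the error-rate consequence is conditional. But the point does not rest on missing detail. Within {14}, a stated figure contradicts the stated inputs. The one-sided 0.025 reading does not rescue it, because alpha is printed as 0.05. And since {20a} does not state sidedness, the phrase "considering a one-sided statistical alternative", together with the directional hypothesis in {7}, is the only guidance a reader has. It could fairly be cited to justify a one-sided test at 0.05.

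**Conclusion.** The text is wrong as written. At the stated rates, alpha and power, 284 per arm is the uncorrected two-sided 5% calculation. The one-sided 5% figure is 224, or 272 with continuity correction. The declared pair of one-sided test and alpha 0.05 does not produce 284 by any standard formula checked.

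The sample size survives: on the protocol's 5% versus 1% assumption, 300 per arm gives 82% power two-sided by normal approximation. The defect is in the error rate and the success criterion. Used as a decision rule, the one-sided label would double the nominal false-positive rate in favour of cholecalciferol, from 2.5% to 5%, and would reverse the conclusion for a narrow band of event counts such as 15 versus 7. Because this criterion governs the primary conclusion, it must be corrected before unblinding.

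**What to change.** In Sample size {14}, delete the one-sided wording and state two-sided alpha = 0.05. In Statistical methods {20a}, state that the primary chi-square test is two-sided at 0.05. Keep 284 as the calculated size and 300 per arm as the enrolment target.

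If the sponsor prefers a directional statement, one-sided alpha = 0.025 in both sections is equivalent for a claim of benefit and leaves the number unchanged. If one-sided 0.05 was truly intended, {14} must instead restate the requirement as 224 per arm (272 with continuity correction) and {20a} must specify the directional test. That route accepts the higher false-positive rate.

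The recommended change costs two sentences and does not alter enrolment, allocation or the choice of test. The only thing given up is the easier one-sided threshold.

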### Recruitment {15}

Males and females 18 to 95 years of age who fulfill the indication criteria for undergoing cardiac surgery by a standardized scoring system (EUROSCORE) can participate in our clinical trial (CT), if they meet the eligibility criteria below (see Table 2). Subjects that are pregnant, breastfeeding, or planning to become pregnant during CT will be excluded. If a subject becomes pregnant during the CT, they will be terminated from the CT medication and will be removed from CT. However, due to the character of the clinical trial and the medication used, it will not be necessary to require women to use contraceptives.

Patients will be admitted to the CT independent of age, gender, race, and type of surgery including sternotomy. Subsequently, initial calcidiol blood concentration will be evaluated for each proposed patient. If the calcidiol blood concentration is below 75 nmol/L, the patient will be offered participation in the CT. By providing signed, informed consent, the patient will become a subject of CT assessment, will receive a CT identification number, and will be subsequently randomized (see Fig. 1).

**Fig. 1 Fig1:**
[figure not shown]
Scheme of clinical trial. Patient who is indicated for heart surgery procedure undergoing sternotomy and its initial serum calcidiol concentration is below 75 nmol/L; he/she becomes an object for enrollment into the CT. If the patient fulfills the inclusion criteria and is not meeting the exclusion criteria at the same time, he/she is offered to participate in the trial. If the patient agrees with the trial participation and signs an informed consent, he/she is randomized

To control for selection bias, a prospective database of patients undergoing sternotomy and not participating in the trial will be maintained at each site during the trial period.

## Assignment of interventions: allocation

### Sequence generation {16a}

Sequence allocation from number 1 up to number 600 was done using R Core Team randomization software (version 2015) with the accompanying information of whether the respective subject receives a placebo or cholecalciferol. The probability that respective identification number is assigned to placebo or cholecalciferol was set within the ratio of 1:1 (in blocks) to ensure approximately even distribution of both compounded investigational medicinal products (placebo/cholecalciferol) in both CT arms.

### Concealment mechanism {16b}

Items in this list have been individually sealed in randomization envelopes labeled with the identification numbers (1–600) on the front side. The sealed envelopes have been placed in a special room unavailable to those who enroll participants or assign interventions. No other restrictions have been used.

### Implementation {16c}

Sequence allocation has been carried out by a certified independent statistician. Patients are enrolled by a clinical trial examiner (medical doctor) and also assigned to interventions. An independent clinical pharmacist (not blinded) receives information about the newly enrolled patient, unseals the new envelope with the respective patient CT number, and gives the compounding instructions for investigational medication to the compounding pharmacist.

Patient randomization is performed by unsealing the randomization envelope labeled with the appropriate identification number at the time when patient is accepted into the CT and has provided signed, information consent (see Fig. 1). Replacement of previously randomized patients by new patients is not permitted during the CT.

## Assignment of interventions: blinding

### Who will be blinded {17a}

Our clinical trial is conducted as double-blind, so neither the investigator and his team (care providers, outcome assessors) nor the trial participants know whether they are using cholecalciferol or placebo, but they know all clinical data about the trial participants.

Only one independent person (clinical pharmacist), who provides instructions regarding the IMP compounding, is unblinded. The pharmacist is only unblinded to the subject identification number and code of the IMP, but otherwise is blinded to clinical data and the patient’s name.

The blinding information is covered in blinding envelopes created by the pharmacist. The blinding envelope contains 4 details: date of IMP compounding, type of IMP (placebo/cholecalciferol), and batch and amount of IMP.

All personal patient data are blinded for data analyses.

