
After the initial bolus, dosing will continue for 26 weeks in weekly intervals, starting from the day that the patient received the first preoperative bolus:
Patient cohort with vitamin D deficiency (calcidiol 0–24 nmol/L) will receive 40 drops per week (2986 IU/day). We expect a 75-nmol/L increase in calcidiol blood concentration in the non-placebo group. The total cumulative vitamin D3 dose is 545,000 IU per 6 months.Patient cohort with vitamin D insufficiency (calcidiol 25–49 nmol/L) will receive 25 drops per week (1917 IU/day). We expect a 50-nmol/L increase in calcidiol blood concentration in the non-placebo group. The total cumulative vitamin D3 dose is 350,000 IU per 6 months.Patient cohort with vitamin D sufficiency (calcidiol level 50–75 nmol/L) will receive 10 drops per week (849 IU/day). We expect a 25-nmol/L increase in calcidiol blood concentration in the non-placebo group. The total cumulative vitamin D3 dose is 155,000 IU per 6 months.

The placebo subjects in each group will receive the same number of drops of inert vehicle (*Triglycerida saturata media*), assuming that the number of drops of placebo does not play a role in placebo efficacy.

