#### Safety outcomes

Safety endpoints related to impaired biochemical examinations, calculated incidence in two parallel patient groups with cholecalciferol or placebo treatment:
Serum calcium concentration out of physiological range (values within the range 2.05–2.9 mmol/L considered physiological)Alkaline phosphatase activity out of physiological range (values within the range 0.66–2.2 μcat/L considered physiological)Serum phosphate concentration out of physiological range (values within the range 0.65–1.61 mmol/L considered physiological)Endpoints related to non-serious adverse effects, calculated incidence in two parallel patient groups with cholecalciferol or placebo treatment:
ConstipationLoss of appetiteNauseaOther non-serious adverse effectEndpoints related to serious adverse events, calculated incidence in two parallel patient groups with cholecalciferol or placebo treatment:
DeathLife-threateningHospitalization (initial or prolonged)Disability or permanent damageRequired intervention to prevent permanent impairment or damage (devices)Important medical event

Efficacy and safety endpoint evaluation timetable is shown in Table 3.

**Table 3 Tab3:** Efficacy and safety endpoint evaluation timetable

Week	Examination of the subject by the investigator	Laboratory examination of the subject	Evaluation of subject’s quality of life	Imaging examination of the subject
**0**	**Initial interview with the patient + initial medical examination + decision to offer clinical trial participation to the patient**	**Initial complete biochemical examination including monitored parameters (calcium, phosphate, calcidiol, and ALP)**	**Acquaintance with the trial + provision of signed informed consent**	
**1**		**Continuous determination of several biochemical parameters during hospitalization: serum calcium (minimally every other day), ALP values (minimally once during hospitalization), and serum phosphate (minimally once during hospitalization)**		
**2**	**Examination of the surgical wound before hospital discharge**	**Laboratory tests before discharge**		
**6**	**Continuous examination of surgical wound**	**Continuous evaluation of serum calcium, ALP, and phosphate**		
**26**	**Exit examination of the surgical wound**	**(1) Final lab. test of serum calcium, ALP, and phosphate; (2) calcidiol level; (3) doctor’s entry in Questionnaire No. 1**	**Final evaluation of quality of life according to Questionnaire No. 2**	**Computed tomography of the chest**

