## Data collection and management

### Plans for assessment and collection of outcomes {18a}

Different outcome investigators are responsible for data collection and assessment (trial examiners, trial clinical biochemist, trial clinical radiologist, trial pharmacists, and trial administrative workers).

There are two electronic databases: Database No. 1 (central trial register) with access for all trial workers except the pharmacist, and Database No. 2 (information about IMP content) with an access restricted to the pharmacist and independent clinical pharmacist.

Trial data from laboratory tests will be copied from hospital patient medical records and stored in one database (Database No. 1) at the end of the clinical trial.

Two paper questionnaires will be used: Questionnaire No. 1 for medical doctor reporting clinical findings and Questionnaire No. 2 for the trial participants. Patient questionnaires and medical assessment questionnaires will primarily be hard copy (paper version), and the data from them will be manually transferred to the central electronic database.

The main clinical trial coordinator is also responsible for clinical trial monitoring.

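### Nothing withholds the routine week-26 calcidiol result from assessors who may know all clinical data, so the final wound examination and CT grade can be unblinded

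*Protocol article*

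**What the plan says.** Section {17a} of the protocol article describes the trial as double-blind: "neither the investigator and his team (care providers, outcome assessors) nor the trial participants know whether they are using cholecalciferol or placebo". The same sentence continues "but they know all clinical data about the trial participants". The one unblinded person, the clinical pharmacist, is by contrast kept from clinical data and from patient names.

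The week-26 row of Table 3 (Safety outcomes) lists three activities:
- under examination, "Exit examination of the surgical wound";
- under laboratory work, "Final lab. test of serum calcium, ALP, and phosphate; (2) calcidiol level", with the doctor's entry in Questionnaire No. 1 in the same cell;
- under imaging, "Computed tomography of the chest".

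The primary endpoint (Outcomes {12}) is judged by inspection, palpation and auscultation, with 6 weeks and 6 months as its evaluation points. The sternal healing grade is read by a radiologist from the month-6 CT.

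For the cohort with baseline calcidiol 0–24 nmol/L, the dosing rationale states: "We expect a 75-nmol/L increase in calcidiol blood concentration in the non-placebo group". It gives matching expectations of 50 nmol/L for baseline 25–49 and 25 nmol/L for baseline 50–75. Baseline calcidiol decides eligibility (Recruitment {15}) and the weekly number of drops (Intervention description {11a}).

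On data flow, {18a} says: "Trial data from laboratory tests will be copied from hospital patient medical records". The sentence goes on to place them in Database No. 1 at the end of the trial. All trial workers except the pharmacist can open that database.

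**The concern.** Serum calcidiol is what the body makes from the study drug, so its change over the trial is a marker of allocation. The plan measures it in every patient in the week of the last outcome assessments. It says that the assessors know all clinical data, and it sets no rule that the result be held back or that the assessments be recorded first. Chronic vitamin D use outside the study drug is prohibited, which makes a large rise point more clearly to active treatment.

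Two outcomes are at stake: the 6-month part of the primary endpoint and the CT healing grade. Both rest on a person's judgement. An assessor who has inferred the arm may examine or grade differently, and the resulting bias cannot be removed in the analysis.

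**Working it through.** **1. Reproduce the plan's own figure.** The rationale for choosing cholecalciferol aims for 75–100 nmol/L in active patients at the end of the trial. Adding each cohort's expected rise to its baseline range gives:
- baseline 0–24: 0 + 75 to 24 + 75 = 75–99 nmol/L;
- baseline 25–49: 25 + 50 to 49 + 50 = 75–99 nmol/L;
- baseline 50–75: 50 + 25 to 75 + 25 = 75–100 nmol/L.

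The target and the expected rises agree, so the rises can be taken as the plan's expected effect on calcidiol.

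**2. How well the result points to the arm.** Suppose the change in calcidiol is normal with the same SD in both arms, allocation is 1:1 (Sequence generation {16a}), and the assessor guesses active when the change exceeds the midpoint between the two arm means. Then

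P(correct guess) = Φ(d / (2·SD)), where d = expected rise on active minus change on placebo.

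Inputs from the article: rises of 75, 50 and 25 nmol/L.
Inputs assumed, because the article does not give them: SD of change 15 to 30 nmol/L; placebo change 0 or +10 nmol/L.

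| Baseline (nmol/L) | Placebo change | d | SD 15 | SD 30 |
|---|---|---|---|---|
| 0–24 | 0 | 75 | Φ(2.50) = 0.994 | Φ(1.25) = 0.894 |
| 0–24 | +10 | 65 | Φ(2.17) = 0.985 | Φ(1.08) = 0.861 |
| 25–49 | 0 | 50 | Φ(1.67) = 0.952 | Φ(0.83) = 0.798 |
| 25–49 | +10 | 40 | Φ(1.33) = 0.909 | Φ(0.67) = 0.748 |
| 50–75 | 0 | 25 | Φ(0.83) = 0.798 | Φ(0.42) = 0.662 |
| 50–75 | +10 | 15 | Φ(0.50) = 0.691 | Φ(0.25) = 0.599 |

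With the result masked, calcidiol gives no information and the chance is 0.50. The result is close to decisive in the lowest cohort, strong in the middle one and only suggestive in the highest. The article does not say how patients divide among the cohorts, so no trial-wide figure can be given.

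**3. Which judgements are exposed.** Table 3 schedules calcidiol at week 0 and week 26 only. The monitoring at week 1 and week 6 covers calcium, ALP and phosphate, and no calcidiol is named for the tests before discharge. Otherwise calcidiol is measured only in a targeted way when overdose is suspected ({11b}). The in-hospital, discharge and week-6 wound assessments are therefore not exposed by this route. The exit wound examination, Questionnaire No. 1 and the CT grade are.

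**The case against.** The other side has several fair points.

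- **Order.** Table 3 lists weeks, not a sequence within a visit. Blood drawn at the exit visit may well be reported after the wound has been examined. The radiologist is listed in {18a} separately from the examiners and the biochemist, and nothing says that the radiologist looks up calcidiol. This stands: unblinding is possible, not shown. It also means that the blind depends on laboratory turnaround rather than on a rule.
- **Data flow.** Laboratory values enter Database No. 1 only at the end of the trial. This closes one route. The source is the hospital medical record, for which no restriction is stated, so the protection is partial.
- **Meaning of the phrase.** In {17a} the words on clinical data contrast the team with the pharmacist and do not set a release rule for one assay. A condensed article may leave such a rule to the full protocol. Silence alone would be excusable. Here, though, the article positively states that the assessors have all clinical data and makes no exception.
- **Other sources of variation.** The article notes that calcidiol also reflects skin production and diet, and it asks patients to report days of sunbathing. This is why the working allows a wide SD and a placebo rise.

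A reader might also infer that the result simply reveals the arm, or that all of the roughly 18 expected events (300 × 0.05 + 300 × 0.01 = 15 + 3) are open to bias. Neither is supported. In the 50–75 cohort the result only shifts the odds. Complications already recorded at discharge or week 6 cannot be altered by a later laboratory value, and the article does not say how many would first be judged at week 26. An event also requires both soft tissue dehiscence and sternal crepitation.

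**Conclusion.** The point holds in a limited form. As written, the plan allows the routine week-26 calcidiol result to reach the people who make the final wound judgement and the CT grading before they make it. If it does, they could guess the arm correctly in about 86–99% of patients with baseline 0–24 nmol/L, 75–95% with baseline 25–49 and 60–80% with baseline 50–75, against 50% when masked. These figures rest on the article's expected rises, the assumed SD of 15 to 30 nmol/L, the assumed placebo change of 0 to +10 nmol/L, normality and a midpoint cut-off.

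The documents do not show that the double-blind has failed, and they give no basis for a figure on how far the primary result could move. The exposure is confined to one time point and depends on an unstated order of events. It is still worth closing, because the affected assessments are subjective and the remedy is cheap.

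**What to change.** Amend {17a} to say that the laboratory withholds the routine week-26 calcidiol result from the examiners, the surgeons, the radiologist and the patient until the exit wound examination, Questionnaire No. 1 and the CT grade have been recorded and locked. Qualify the statement that the team knows all clinical data to match.

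Leave the targeted calcidiol testing for suspected overdose in {11b} as it is. Do not route the results through the unblinded clinical pharmacist: {17a} keeps that person from clinical data and {18a} bars the pharmacist from Database No. 1, so doing so would break a separation that the plan has deliberately made.

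The cost is a reporting flag in the laboratory and a sentence or two in the protocol. No visit, test or sample-size figure changes. The downside is that the routine final value reaches the clinician slightly later.
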